## Abstract

**Background:**

Excessive and inappropriate use of antibiotics is the most important driver of antimicrobial resistance. The aim of the HAPPY PATIENT project is to evaluate the adaptation of European Union (EU) recommendations on the prudent use of antimicrobials in human health by evaluating the impact of a multifaceted intervention targeting different categories of healthcare professionals (HCPs) on common community-acquired infectious diseases, especially respiratory and urinary tract infections.

**Methods/design:**

HAPPY PATIENT was initiated in January 2021 and is planned to end in December 2023. The partners of this project include 15 organizations from 9 countries. Diverse HCPs (doctors, nurses, pharmacists, and pharmacy technicians) will be audited by the Audit Project Odense (APO) method before and after an intervention in four different settings: general practice, out of hours services, nursing homes and community pharmacies in four high antibiotic prescribing countries (France, Poland, Greece, and Spain) and one low prescribing country (Lithuania). About 25 individuals from each professional group will be recruited in each country, who will register at least 25 patients with community-acquired infections during each audit period. Shortly before the second registration participants will undertake a multifaceted intervention and will receive the results from the first registration to allow the identification of possible quality problems. At these meetings participants will receive training courses on enhancement of communication skills, dissemination of clinical guidelines with recommendations for diagnosis and treatment, posters for the waiting rooms, and leaflets for patients. The results of the second registration will be compared with those obtained in the first audit.

**Discussion:**

HAPPY PATIENT is an EU-funded project aimed at contributing to the battle against antibiotic resistance through improvement of the quality of management of common community-acquired infections based on interventions by different types of HCPs. It is hypothesized that the use of multifaceted strategies combining active intervention will be effective in reducing inappropriate prescribing and dispensing of antibiotics.

**Study registration:**

EU Health programmes project database https://webgate.ec.europa.eu/chafea_pdb/health/projects/900024/summary; date of registration: 1 January 2021.

## Background

Excessive antibiotic use is considered to be the main driver of the growing development and spread of antimicrobial resistance (AMR) [1]. Infections caused by resistant bacteria are challenging as they can lead to increased mortality, prolonged hospital stays and higher medical costs [2, 3]. Countries with inappropriate and high use of antibiotics, such as the southern and eastern European countries, have a high rate of resistance [4]. As antibiotic resistance spreads across borders, high prevalence countries serve as a source of bacterial resistance for countries with a low prevalence [5]. Therefore, AMR is an important issue with a potentially serious impact on all countries.

The most effective measure to curb the problem of AMR is to reduce the unnecessary prescriptions of antibiotics is [6]. Most antibiotics in general practice (more than 80%) are prescribed for respiratory tract infections (RTI) and urinary tract infections (UTI) [7, 8]. Therefore, community-acquired infections (CAI) should constitute the main target of stewardship strategies. The development of detailed guidelines by the European Union specifically related to the prudent use of antimicrobials in humans (the EU AMR Guidelines) has ushered in a new phase of the overall strategy [9]. To intensively engage key stakeholders, it is necessary to increase knowledge and implement the EU AMR Guidelines and reduce the demand and prescription of antibiotics in inappropriate cases. In order to change both prescribing and dispensing habits and patient expectations stakeholders must be asked to re-evaluate well-established practices. The evidence shows that just delivering guidelines is not enough to restrict antibiotic prescribing [10]. Changing practice behaviour is challenging and requires the implementation of a systematic approach following components of the normalization process theory (NPT), in which individual and group reflection of the actions that need to be implemented to reduce inappropriate prescribing of antibiotics will secure the achievement of high impact and sustainable results [11].

Previous results of similar studies aimed at decreasing the inappropriate use of antibiotics have demonstrated that a reduction mainly depends on the context and the components of the multifaceted intervention. In the HAPPY AUDIT project, 440 general practitioners (GP) from six countries registered 47,011 consultations before and after an intervention including individual prescriber feedback, training courses, clinical guidelines, posters for waiting rooms, patient brochures and access to two different point of care tests [12]. After the intervention, clinicians significantly reduced the percentage of consultations resulting in antibiotic prescription, and in patients with lower RTIs, doctors reduced the prescribing rate by a percentage ranging from 42% in Lithuania to 9% in Argentina. In a quality control-based randomised clinical trial carried out in four South American countries, the clusters of practices assigned to the intervention groups reduced antibiotic prescribing rates from 37.4 to 28.1% in patients diagnosed with either acute otitis media or acute bronchitis, whereas the reduction in the control group was marginal, from 29.0 to 27.2% [13].

In the HAPPY PATIENT project, the interventions will be carried out in five countries with different cultural backgrounds and different organisations of healthcare: Greece, France, Spain, Poland, and Lithuania. This will ensure better generalisation of the results to a wide range of settings and different healthcare organisations. Table 1 describes the differences across these five countries [14]. In terms of antibiotic consumption, the first four countries have high levels of antibiotic consumption and according to the latest statistics on antibiotic prescribing in the primary care setting in 2020 these countries ranked in the first quartile, while Lithuania has a relatively low consumption level, that is under the European mean [7]. The project also analyses the dispensing process, as pharmacists play a crucial role in directly reinforcing messages about appropriate use when dispensing antibiotics to patients or carers and are amongst the groups most trusted to convey such messages.

**Table 1 Tab1:** Characteristics of the health care systems in the HAPPY PATIENT project target countries

	France	Greece	Lithuania	Poland	Spain
Population (million)	66.9	10.7	2.8	38.4	46.7
Proportion of population 65+ (%)	19.8	21.9	19.7	17.2	19.3
Percentage of the gross domestic product to health	11.3	8.0	6.5	6.5	8.9
Number of doctors in practice per 1000 inhabitants	3.2	6.3	4.6	2.4	3.9
Number of nurses in practice per 1000 inhabitants	10.8	3.3	7.7	5.1	5.7
Predominant mode of provision	Private	Public	Public	Public	Public
Copayment of patients in primary care	Yes	No, public providers	No	No	No
Copayment of patients in prescriptions	Yes	Yes	Yes	Yes	Yes
Organisation in primary care	Groups of GPs and other HCPs or single-handed practices	Groups of GPs and other HCPs	Groups of GPs and other HCPs	Individual and group GPs and other HCPs	Groups of GPs and other HCPs
The patient must be registered with a GP	No, but they have advantages if registered	No	Yes	Yes	Yes
Freedom of choice of GP	Yes	Yes	Yes	Yes	Yes
Gatekeeping. GP referral requirement	For some specialist care	Not required	For most specialist care	For some specialist care	For most specialist care
Remuneration of GPs	Mix of salary, payment for service, and capitation	Mix of salary and payment for services	Mix of payment for services and capitation	Mix of capitation and payment for services	Mix of salary and capitation
GP mean income per year (in euros)	50,263	25,000	10,782	38,400	45,000
Average population size per GP	864	–	1550	1539	1500
Frequency of GP medical consultations per inhabitant and year	6.0	4.2	6.6	6.6	3.0
Status of long-term care providers	Mixed provider status: public (58%); not-for-profit organizations (religious groups, corporate org.) (26%); private (16%)	Mixed provider status: public sector (appr. 1/3); private, mainly for-profit and some not for-profit (ie. church charitable org. and local authorities) (appr. 2/3)	Mixed provider status: public (appr. 50%); private (appr. 50%)	Mixed provider status: public (appr. 70%); private sector (appr. 30%)	Mixed provider status: public (26.6%); private (71,9%)
Number of pharmacies per 100,000 inhabitants	33	88	40	36	47

*GP* General Practitioner, *HCP* Health Care Professional. Data from 2018

## Methods/design

### Aims of the study

The overall goal of the HAPPY PATIENT project is to increase the impact of EU recommendations on the prudent use and dispensing of antimicrobials in human health through a focus on critical interaction between patients and HCPs, evaluating the impact of a multifaceted intervention on their antibiotic prescribing or dispensing in four different settings.

### Design

HAPPY PATIENT was initiated in January 2021 and the project is planned to finish in December 2023. The project includes 15 partners from nine countries, as indicated in Table 2. The Audit Project Odense (APO) methodology is used [15], which is an evidence-based multifaceted intervention to improve quality of care by implementing guidelines [16]. This is a before and after intervention study, with two audit registration periods (Fig. 1). A minimum number of 25 HCPs will be recruited in each setting and will collect CAIs during a first audit registration in February 2022. In autumn 2022, the four groups of HCPs will be invited to a face-to-face meeting to receive a multifaceted intervention. In February 2023, the same participants will register the same type of CAIs for a second audit.

**Table 2 Tab2:** Partners in HAPPY PATIENT

Participant organisation name	Abbreviation	Role
Institut Català de la Salut and Fundació Institut Universitari per a la Recerca a l’Atenció Primària de Salut Jordi Gol	ICS/IDIAP	Coordinator of the project. Spanish network
University of Copenhagen	UCPH	Co-design and consensus methodology
Research Unit for General Practice Odense	RUPO	APO methodology. Primary healthcare settings
NORCE Norwegian Research Centre AS	NORCE	Out of hours settings
The Capital Region of Denmark	CAPREG	Nursing homes settings
Rijksuniversiteit Groningen, The Netherlands	RUG	Pharmacy settings
University of Las Palmas de Gran Canaria and Fundación Canaria Parque Científico Tecnológico	ULPGC/FCPCT	Analysis and evaluation of the results
Spanish Society for Family and Community Medicine	SEMFYC	Dissemination and training in communication skills
Nice University Hospital	CHUNICE	French network
Ltd Mano Seimos Gydytojas (My Family Doctor)	FDC	Lithuanian network
Medical University of Lodz, Poland	MUL	Poland network
University of Crete, Greece	UOC	Greek network
European Association for Clinical Pharmacology and Therapeutics	EACPT	Advisor
Rennes University Hospital, France	CHURE	Advisor
University Institute for Patient Care, Spain	UIC	Advisor

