### Phase 2: audit registrations

The project will conduct two audit registrations: the first will begin before the intervention (February 2022) and the second will take place after the intervention (February 2023). The same month has been chosen for the implementation of both registrations to minimize the effect of potential seasonal variation in CAIs. A registration pilot testing, in November 2021 with approximately five HCP participants per setting and per country, ensured that the content of the registration chart was relevant to their practice and easily understood, and confirmed that sufficient patients could be recruited.

During the audit period the participants will use the APO registration chart to record all consultations or dispensations regarding the CAIs selected for audit. Participants will be asked to fill in the chart with the consecutive consultations they receive regarding the CAIs selected, and in the case of pharmacies, all the systemic antibiotic dispensations given for acute infections. A specific registration chart for each of the 4 settings has been developed considering their characteristics and the quality improvement areas that HAPPY PATIENT seeks in each setting. The example of the template used in nursing homes is depicted in Fig. 2. At most, 10 main domains and a maximum of 45 variables are used to describe the topic investigated. The main domains are lined up in a logical way; for example: type of contact, symptoms present, examinations performed, diagnosis, treatment, and assessment. According to the APO methodology the variables are exhaustive (include all possibilities) and exclusive (no overlapping), and all follow the same logic plan. One line is filled in for each registered case and, as a general rule, only multiple choice is allowed (no open-ended text). At least one choice per main group is needed. A short instruction sheet will be provided for all HCP participants, with details about the registration period, the inclusion and exclusion criteria for the cases and a brief explanation of the content of each main group.

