### Statistical analysis plan

Statistical methods for inference in small samples will be used according to a statistical analysis plan. The minimum number of HCPs per APO audit cycle has been estimated based on the assumption that each HCP will register about 25 cases, including either consultations or dispensations, during the audit registration. A decrease of 15% in antibiotic prescribing can be expected after the intervention (from about 40% before to about 25% after). The within-practice correlation coefficient is 0.1. If the comparison is to be performed at the 5% level of significance (two-sided) with 80% power, then the number of HCPs to be included should be 25 per APO cycle. There will be 20 APO cycles in the project (one for each of the 4 healthcare settings involved in each of the 5 target countries). We assume the participation of 500 HCPs in the project and the registration of 25,000 cases.

We will apply the Fisher exact test to the frequencies of prescriptions before and dispensations before and after the audit for each group of professionals and setting/country to test the null hypothesis of no effect of the audit. We will also estimate the effect of the interventions with logistic two-level regression models: a) cases of CAIs and b) HCP participants. Antibiotic prescription will be considered as the dependent variable (yes/no) as well as the concepts of inappropriate prescribing and inappropriate dispensing. These models control for symptoms and duration, as well as for the demand for antibiotics by the patient. Goodness of fit will be assessed using the Wald test of the model, with the deviance test to compare alternative models. Statistical significance will be considered with *P* < 0.05. The data will be analysed using Stata v16.

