### Ethics and dissemination

The study will be conducted in accordance with the protocol, the Declaration of Helsinki, the principles of Good Clinical Practice, The General Data Protection Regulation (EU) 2016/679 and the Human Research Act as well as other locally relevant regulations. This project has an Ethical Advisor that prepared the necessary documents to submit the project to the Ethics Committee Boards of the different participating countries. The Ethical Committee Boards of Greece and Spain deemed necessary to review the project and gave their favourable opinion. In Lithuania, Poland and France there was no need for the Ethical Committee to review this type of projects. This was confirmed by the national coordinators together with their Ethical Committee Boards.

HCPs will be contacted by local coordinators who will explain the study and hand over the information sheet to the professional, giving the professional time to read it and ask any questions. If HCPs accept to take part in the study, they will sign the consent form before participation. Participants will be able to withdraw from the project at any time without giving any explanation.

Information gathered from the patient consultations or dispensations will be personal non identifiable data (only age in years and sex will be recorded) and the minimum data set necessary for the study will be collected. No intervention or follow-up will be performed in the patients except for the distribution and discussion of leaflets on infections. Data will be anonymised from the beginning, coded in the template with the code of the HCP and a consecutive number for each consultation or dispensation. There will be no intervention, no follow-up and no documents that link the patient information with its code. Therefore, individual patient consent is not required. The HAPPY PATIENT project is an intervention study targeting HCPs to improve their performance according to good clinical practice and it does not involve any risk to the HCPs nor the patients whose CAI consultation or dispensation data are collected. Therefore, insurance is not needed for the HAPPY PATIENT project.

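### An uncontrolled before-after change is tested as an effect of the audit, and the stated model covariates leave out recorded age and sex and a broad infection group

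*Protocol article*

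**What the plan says.** The Design section declares the structure openly: "This is a before and after intervention study, with two audit registration periods". The same professionals take part twice ("In February 2023, the same participants will register the same type of CAIs for a second audit"), but each audit registers its own patients. The abstract gives the contrast: "The results of the second registration will be compared with those obtained in the first audit". No concurrent control group is described.

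Against change over time, the article offers the repeated participants and the calendar month: "The same month has been chosen for the implementation of both registrations to minimize the effect of potential seasonal variation in CAIs".

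The Statistical analysis plan section gives two analyses:

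- An unadjusted test by professional group and setting/country: "We will apply the Fisher exact test to the frequencies of prescriptions before and dispensations before and after the audit". Its null hypothesis is worded as the absence of an audit effect.
- Two-level logistic models (cases within professionals), said to estimate the effect of the interventions. On covariates: "These models control for symptoms and duration, as well as for the demand for antibiotics by the patient".

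Under Ethics and dissemination, the article says of patients' personal data that "only age in years and sex will be recorded". Diagnosis appears among the example chart domains under Phase 2: audit registrations.

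The Limitations section covers volunteer participants, the Hawthorne effect, diagnostic misclassification and unmeasured non-biomedical factors. It is silent on the missing control and on differences between the two years.

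**The concern.** A before-after contrast with new patients in each period measures the sum of three things: any effect of the intervention, background change in prescribing, and change in the mix of patients. Using the same month deals with season within a year. It does not deal with a difference between one February and the next. The Fisher test cannot separate the three parts, yet its null is phrased as if only the first existed.

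The models can remove the measured part of a case-mix change, but only for the variables they contain. Age and sex cost nothing to add because they are already on the form. The same holds for a broad RTI/UTI split where the chart records diagnosis.

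What is at stake is the wording of the main conclusion: a change between two audits, or an effect of the audit.

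**Working it through.** **The plan's own figure.** Inputs from the Statistical analysis plan section: 40% before, 25% after, two-sided 5%, 80% power, correlation 0.1, 25 cases per professional.

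- Design effect: 1 + (25 − 1) × 0.1 = 3.4.
- Two-proportion sample size: 152 per audit, or 165 with continuity correction.
- Professionals: 152 × 3.4 / 25 = 20.7, so 21; with correction 165 × 3.4 / 25 = 22.4, so 23.

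The stated 25 is close to this and is not disputed. One cycle therefore has 25 × 25 = 625 cases per audit.

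**Case-mix illustration.** The documents give no prescribing rates by infection, so the following are assumptions: UTI treated in 85%, UTI share 20% in the first audit, overall rate 40% as planned, and no change in behaviour.

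- Implied RTI rate: (0.40 − 0.20 × 0.85) / 0.80 = 0.2875.
- Second-audit rate for UTI share s: 0.85s + 0.2875(1 − s).

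| UTI share, second audit | Overall rate | Apparent fall | Counts of 625 | Unadjusted Fisher P |
|---|---|---|---|---|
| 18% | 38.9% | 1.1 points | 250 v 243 | 0.73 |
| 15% | 37.2% | 2.8 points | 250 v 232 | 0.32 |
| 10% | 34.4% | 5.6 points | 250 v 215 | 0.047 |

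Against the planned 15-point fall, these are 1.125/15 = 7.5%, 2.8125/15 = 19% and 5.625/15 = 37.5%. Only the halved share reaches nominal significance. Even that result ignores clustering: with an effective 625/3.4 = 184 cases per audit, z = 0.05625 / √(2 × 0.3719 × 0.6281 / 184) = 1.12, so P is about 0.26.

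**Does stratifying help?** A simulation assumed two diagnosis groups with equal shares in the first audit, no true effect, 625 cases per audit and no clustering.

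| Assumed rates | Fall in high-rate share | Apparent fall | Fisher rejects | Mantel-Haenszel by group rejects |
|---|---|---|---|---|
| 60% / 20% | 10 points | 4 points | 29% | 5% |
| 60% / 20% | 20 points | 8 points | 83% | 5% |
| 70% / 10% | 10 points | 6 points | 57% | 5% |
| 70% / 10% | 20 points | 12 points | 99% | 5% |

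Conditioning on the group restores the nominal level for measured mix. It does nothing for background trend or unmeasured change.

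**Background change in the article's own evidence.** For the South American randomised trial, the Background section reports a fall in the intervention group of 37.4 − 28.1 = 9.3 points. Of the controls it says: "whereas the reduction in the control group was marginal, from 29.0 to 27.2" per cent, a fall of 1.8 points. A before-after reading would have credited 9.3 points; the controlled difference is 9.3 − 1.8 = 7.5. That trial concerned otitis media and bronchitis elsewhere, so 1.8 is not a forecast for this study. It shows only that the background part need not be zero.

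**The case against.** The strongest reply has four parts.

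1. **The models already adjust for case mix.** They include symptoms, and the charts collect typical RTI and UTI signs, which largely separate the two sites. This stands. A reader might infer that a shift in case mix passes in full into every reported effect. That is true of the Fisher test only; in the models the remainder is smaller, and its size cannot be worked out from the documents. The illustration above is unadjusted and says nothing about the size of bias in the models.

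2. **The covariate list belongs to an analysis plan that is not shown.** This stands in part. A fuller list there could cure the covariate point. It would not cure the article's causal null or its limitations section. It is also certain only that age and sex are recorded; infection group is inferred from an example domain, and charts differ by setting.

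3. **Background drift is small at the planned level of testing.** A reader might pool all 20 cycles and note that 29.0% v 27.2% with 12,500 cases per audit gives P of about 0.002. The documents do not support that use. Fisher is planned by setting/country, where 625 per audit gives P = 0.53. Pooling with the design effect of 3.4 gives about 0.09, and the pool would include pharmacies, which register dispensations rather than prescribing decisions.

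4. **The design is declared, and covariates do not replace a control.** Both are true, which is why the wording has to change as well. It may be tempting to require a benchmark against national monthly antibiotic statistics. Nothing in the documents shows that such figures exist by month and setting, and consumption is not prescribing per registered consultation.

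**Conclusion.** The point holds in limited form. The contrast is uncontrolled, the Fisher null is worded causally, the limitations do not acknowledge this, and the stated covariates leave out age, sex and broad infection group. On the assumed rates, case mix alone could move unadjusted prescribing by about 1 to 6 points against a planned 15. The upper end needs the UTI share to halve, and the nominal P of 0.047 there does not survive allowance for clustering. These sizes rest on rates and shares that the documents do not give. The case for acting is that the remedy is nearly free and changes what the study may conclude, not that a large bias has been shown. It should be corrected before the analysis.

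**What to change.** - In the prescribing models for general practice, out-of-hours services and nursing homes, add age, sex and broad infection group (RTI/UTI). Use the broad group because the Limitations section warns that clinicians may fit a specific diagnosis to the treatment decision. Pharmacy outcomes differ and are not part of this change.
- Report case mix by audit, and give results separately for RTI and UTI.
- Make the adjusted model, not the Fisher test, the basis for conclusions.
- Restate the null hypothesis as no change between the two audits.
- Add the missing concurrent control and possible change between years to the limitations, and word conclusions as before-after change.

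The cost is a few model terms, one descriptive table, some extra subgroup output and slightly more cautious conclusions. For age and sex no new data are needed; the same holds for infection group where the chart records diagnosis.
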